### Phase 3: Pilot Randomized Controlled Trial

#### Study Design

A pilot RCT will be conducted at 2 iTech SRVs (Boston, MA, and Bronx, NY) to evaluate the feasibility and acceptability of the MyChoices app and examine the preliminary efficacy of the app in increasing HIV testing and PrEP uptake compared with a standard of care control group. This information will determine whether MyChoices moves forward to be tested in a full-scale efficacy trial planned with iTech. We will enroll 60 YMSM across 2 iTech SRVs who will be randomized to receive either the MyChoices app or standard of care. Participants will be followed for 6 months and will complete a Web-based assessment every 3 months (Figure 2).

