#### Randomization

Only participants who express interest in using MyChoices for HIV prevention, meet eligibility criteria, provide informed consent, and complete a baseline assessment will be eligible for randomization (see Figure 2). Randomization will be stratified by SRV [31] and will occur in a 2:1 ratio with 40 YMSM randomized to the experimental condition (20 at each SRV) and 20 randomized to the control condition (10 at each SRV). This allocation will allow us to efficiently gather additional data on app utilization. Randomization will be based on a pregenerated list created by the iTech Analytic Core statisticians, with random blocks of size 3 or 6, and will be accessed through a Web portal.

Men who are randomized to receive MyChoices will be given brief instructions on the purpose of the app, how to access it, and an overview of how to use it. Participants will be encouraged to explore all components of the app and use it routinely.

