#### Data Collection

Baseline assessments will be conducted at the enrolling clinical site using CASI, with all follow-up assessments at 3 and 6 months conducted off-site and through Web. At each major assessment, participants will complete a CASI-based assessment battery via a secure Web-based data entry system. Outcome domains and measures are described in Table 1.

**Table 1 table1:** Outcomes and measures for MyChoices pilot randomized controlled trial.

Domain			Description or scale

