### Statistical Analyses

The primary analyses will summarize acceptability (mean score on the SUS) and feasibility (participants utilizing the app at least once during follow-up) of the app, overall for the intervention arm, with asymptotic normal 95% CIs. Point estimates for mean acceptability ≥50 and for proportion accessing the app >0.60 will be considered the minimum criteria for acceptability and feasibility, consistent with industry standards [28,32].

The primary efficacy analysis will compare HIV testing (defined by the proportion that self-reports at least 1 HIV test result during follow-up) between the study arms at 3- and 6-month follow-ups. Group differences in self-reported PrEP-related appointments and documented HIV test results will also be examined at each time point. Moreover, group differences in measures related to the SCT model constructs (eg, HIV testing self-efficacy) will be assessed. The distribution of all variables will be assessed, and appropriate tests will be conducted (ie, parametric chi-square test vs nonparametric Fisher’s exact test).

All analyses will use two-tailed tests of significance, with significance at alpha=.05. We will follow an intent-to-treat approach [52], analyzing participants in the study arm to which they were assigned. We will examine the equivalence of random assignment to groups with regards to key baseline characteristics, including sociodemographics, prior HIV testing patterns, and sexual risk-related variables. In the event that randomization does not work to balance these characteristics, we will assess whether baseline differences may account for differences in outcomes.

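### Randomization is stratified by SRV, but the named between-arm tests ignore it and adjustment waits on an observed imbalance: a modest, avoidable loss of precision

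*Protocol article*

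**What the plan says.** **Design.** Under Randomization: "Randomization will be stratified by SRV [31] and will occur in a 2:1 ratio". The planned arms are 40 app users and 20 controls, split evenly so that each SRV contributes 20 and 10 respectively; block sizes vary between 3 and 6. Table 1 lists SRV or city among the structural covariates.

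**Tests.** Statistical Analyses compares self-reported HIV testing between arms at 3 and 6 months and calls this the primary efficacy analysis. It adds group differences in PrEP-related appointments, documented HIV test results and the social cognitive theory (SCT) constructs, with HIV testing self-efficacy as the example. It then states: "The distribution of all variables will be assessed, and appropriate tests will be conducted (ie, parametric chi-square test vs nonparametric". The nonparametric option that it goes on to name is Fisher's. Tests are two-sided at 0.05.

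**Baseline variables.** The same section checks balance on sociodemographics, prior testing and sexual risk. Only if balance fails will it assess whether baseline differences explain the outcome differences. SRV and the SCT scales are not among the examples given.

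**Data available.** Data Collection describes a baseline assessment by CASI and adds: "At each major assessment, participants will complete a CASI-based assessment battery via a secure Web-based data entry system". Together with Table 1 this implies, without saying so outright, that the SCT scales are taken at baseline.

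**The concern.** A factor used to stratify the randomization is normally carried into the analysis. If it predicts outcome, the blocks remove between-site variation from the arm difference, but a pooled test still counts that variation in its standard error. The test then rejects too rarely.

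The article's one route to adjustment does not help. It opens only on an observed imbalance, and stratified blocks largely prevent imbalance in SRV. A rule triggered by the observed data is also less clean than a prespecified model.

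A second mismatch concerns the scales. Chi-square and Fisher tests suit categorical outcomes. The *ie* in the parenthesis reads as an exhaustive list, and it follows directly on the SCT comparison. Self-efficacy and perceived-risk scores would have to be categorized to fit, and nothing commits the plan to using their baseline values.

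What is at stake is precision in the preliminary efficacy estimates, with only 20 controls.

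**Working it through.** **1. Allocation.** Total 60 (Study Design), 2:1 within two SRVs: 60 × 2/3 = 40 and 60 × 1/3 = 20, halved to 20 and 10 per SRV. This reproduces the article's figures. Each arm draws half its members from each SRV, so the crude difference in proportions weights the sites equally in both arms and is unbiased.

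**2. Why the pooled test is conservative.** For site rates p₁ and p₂ with mean p̄, the true standard error relative to the one the pooled test uses is

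r = √{ [p₁(1−p₁) + p₂(1−p₂)]/2 ÷ [p̄(1−p̄)] }.

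- 30%/50%: √(0.23/0.24) = 0.979
- 20%/60%: √(0.20/0.24) = 0.913

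Asymptotic size is 2[1 − Φ(1.96/r)]: 0.045 and 0.032.

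**3. Exact size and power, HIV testing.** The article gives no site-specific testing rates, so these are assumptions shown over a range. All binomial outcomes for 20+20 against 10+10 were enumerated. The stratified statistic (CMH, no continuity correction) is

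[Σ(aₖ − 20mₖ/30)]² ÷ Σ[20·10·mₖ(30−mₖ)/(30²·29)],

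where aₖ is the number tested in the app arm and mₖ the number tested in both arms at site k; it is referred to chi-square on 1 df. Power is for +30 points at both sites.

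| Control rates by site | Size: chi-square / Fisher / CMH | Power: chi-square / Fisher / CMH |
|---|---|---|
| 40%/40% | 0.052 / 0.034 / 0.051 | 0.621 / 0.553 / 0.622 |
| 35%/45% | 0.051 / 0.033 / 0.051 | 0.621 / 0.553 / 0.624 |
| 30%/50% | 0.047 / 0.031 / 0.050 | 0.623 / 0.553 / 0.635 |
| 25%/50% | 0.044 / 0.030 / 0.049 | 0.622 / 0.530 / 0.640 |
| 20%/60% | 0.033 / 0.021 / 0.051 | 0.629 / 0.555 / 0.705 |

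The gain from stratifying is about 1 point of power at a 20-point site gap and about 8 points at a 40-point gap.

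**4. Sparse outcome.** The Background section gives 6% PrEP ever-use at ages 18-24. Taking 6% as control uptake at both sites (an assumption) and +30 points, power is 0.793 for chi-square and 0.786 for CMH. At 5%/15% it is 0.736 and 0.725. Stratifying brings no gain here, and the real strata would be smaller because the outcome is limited to those with a behavioral indication.

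**5. Scale scores.** With baseline-to-follow-up correlation ρ (assumed), ANCOVA multiplies the residual variance by 1 − ρ². Power at a standardized difference of 0.6 (assumed) is Φ(0.6/[√(1−ρ²)·√(1/40 + 1/20)] − 1.96); without adjustment it is Φ(2.191 − 1.96) = 0.59.

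| ρ | Variance cut | SE cut | Equivalent N, 60/(1−ρ²) | Power |
|---|---|---|---|---|
| 0.3 | 9% | 5% | 66 | 0.63 |
| 0.5 | 25% | 13% | 80 | 0.72 |
| 0.7 | 49% | 29% | 118 | 0.87 |

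**6. Does omitting the baseline score distort size?** No. In 40,000 simulated trials with ρ = 0.6 and no site effect, an unadjusted t-test had size 0.051. A site shift of 0.5 or 1.0 SD lowered it to 0.043 or 0.029, so only the ignored stratification factor matters, and again in the conservative direction.

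**The case against.** - **The pilot disclaims power.** The hypotheses and Secondary Outcome Measures both say it is not powered for behavioral outcomes. The stated criteria, mean SUS of at least 50 and more than 60% opening the app, concern the intervention arm alone. This stands and limits the weight of the point. Study Design does include preliminary efficacy in the information that decides whether the app moves forward, but it sets no between-arm threshold.
- **Large site gaps are speculative.** Both SRVs apply the same eligibility criteria, which exclude recent testers, and nothing in the article suggests a 30- or 40-point gap. At plausible smaller gaps the loss is slight. This stands.
- **Detail belongs in the SAP.** Model form and covariates are often left there, and Table 1 does list SRV as a covariate. This stands only in part, because the article did not stay silent: it named the tests with *ie*, and it fixed a trigger for using baseline variables that will hardly ever reach SRV.
- **No test is clearly fixed for the scales.** The parenthesis can be read as covering categorical outcomes only, with the scales left to appropriate tests. That is fair. The wording is then ambiguous rather than a commitment to a wrong test.
- **Fisher's test has a use.** Deleting it would remove the only stated small-sample option. This stands, and the fix keeps an exact test.

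A reader might also infer that the tests are mis-sized in a way that threatens false positives. The documents do not support that. Ignoring SRV makes the tests conservative, and only if SRV is prognostic; leaving out baseline scores costs precision, not validity.

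**Conclusion.** The point holds as a matter of efficiency. The stated tests do not use the stratification factor, and adjustment depends on an imbalance that the design largely prevents. The between-arm comparison stays unbiased.

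The cost for HIV testing runs from nothing at equal site rates, through about 1 point of power at a 20-point gap, to about 8 points at a 40-point gap. All of this rests on assumed site rates and a 30-point effect. For PrEP uptake there is no gain to be had from stratifying. The larger potential gain is in the self-reported SCT scales, with 9% to 49% less variance for an assumed correlation of 0.3 to 0.7, provided the scales are indeed collected at baseline.

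The point touches secondary and tertiary comparisons only. The acceptability and feasibility estimates are unaffected.

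**What to change.** Prespecify the following, to apply whatever balance is observed:

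1. **HIV testing:** a Mantel-Haenszel risk difference and test stratified by SRV.
2. **Sparse outcomes such as PrEP uptake:** keep an exact test, either stratified by SRV or Fisher's.
3. **Self-reported SCT scales measured in both arms** (perceived risk; testing, PrEP and condom self-efficacy): ANCOVA on the follow-up score with arm, baseline score and SRV. App-use measures exist in one arm only and stay descriptive.
4. **Wording:** replace the *ie* clause with text that does not limit the tests to chi-square and Fisher, and state that the SCT scales are collected at baseline, if they are.

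The cost is analysis wording only. SRV is recorded already, the baseline battery appears to be in place, and neither sample size nor visits change.

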	**Structural**		
		SRV^c^ or city	Geographic location of study participant
		Incarceration history	Recent history and frequency
		Structural discrimination	External homophobia [42], racism [47]
		Stigma	HIV-related, PrEP-related

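### Randomization is stratified by recruitment site, but the between-arm tests named do not use site; this costs power only if the two cities differ widely in HIV testing (minor)

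*Protocol article*

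**What the plan says.** **Design.** The Randomization section of the protocol article states: "Randomization will be stratified by SRV [31] and will occur in a 2:1 ratio with 40 YMSM randomized to the experimental condition (20 at" each site, with "20 randomized to the control condition (10 at each SRV"). The list is built "with random blocks of size 3 or 6", so each city stays close to 2:1 throughout enrolment.

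**Analysis.** Statistical Analyses covers the arm comparisons of HIV testing, PrEP-related appointments, documented test results and the social cognitive theory (SCT) measures with one sentence on tests: "The distribution of all variables will be assessed, and appropriate tests will be conducted (ie, parametric chi-square test vs nonparametric" Fisher's exact test. Tests are two-sided at .05. Site is not mentioned.

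**Site elsewhere.** Table 1 lists site or city as a structural covariate ("Geographic location of study participant"), but no analysis is tied to it. The only adjustment foreseen is in Statistical Analyses and is triggered when baseline characteristics turn out unbalanced.

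**Standing of these comparisons.** Table 1 places HIV testing and PrEP uptake among the secondary outcomes, and the article says the pilot is not powered for behavioral outcomes. The stated minimum criteria (mean System Usability Scale score of at least 50, app use above 0.60) are point estimates in the intervention arm alone.

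**The concern.** Stratifying by site removes chance differences in city mix from the arm comparison. A test on a single pooled 2x2 table does not know this. It still counts the difference between cities as random variation, so when city predicts the outcome it judges the arm difference against too large a variance. The actual type I error then falls below .05, and power is lower than a test that uses site would have.

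The imbalance rule does not help. It reacts to factors that randomization failed to balance, and site is the one factor balanced by construction.

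City could matter here, since both arms are referred to local testing and prevention services. With 40 against 20 participants, there is little precision to spare.

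**Working it through.** **Inputs from the article.** "We will enroll 60 YMSM across 2 iTech SRVs"; 2:1 allocation, so 60 × 2/3 = 40 and 60 × 1/3 = 20, or 20 and 10 per site. The stated split is consistent. Tests are two-sided at .05. No power or effect size is given for the arm comparisons, so there is no planned power figure to reproduce.

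**Assumptions.** The mean control rate of HIV testing over the two cities is 40%, anchored on the Background statement that about 60% of YMSM do not test annually. City gaps run from 0 to 40 points around that mean, the effect is +20 or +30 points in both cities, and there is no dropout.

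**Step 1: variance of the arm difference under no effect.**
- As the pooled test sees it: p̄(1 − p̄)(1/40 + 1/20) = 0.40 × 0.60 × 0.075 = 0.0180, standard error 0.134.
- Actual, under allocation fixed by site, cities at 20% and 60%: mean of p(1 − p) = (0.16 + 0.24)/2 = 0.20; 0.20 × 0.075 = 0.0150, standard error 0.122. Ratio √(0.0180/0.0150) = 1.10.
- Cities at 25% and 55%: (0.1875 + 0.2475)/2 = 0.2175; ratio √(0.24/0.2175) = 1.05.
- Cities at 30% and 50%: (0.21 + 0.25)/2 = 0.23; ratio √(0.24/0.23) = 1.02.

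**Step 2: exact type I error and power.** All 21 × 11 × 21 × 11 = 53,361 outcomes of the two site tables were enumerated with their binomial probabilities. The CMH statistic, without continuity correction, is [Σ(a − 20m/30)]² / Σ[20·10·m(30 − m)/(30²·29)]. The sums run over sites, a is app-arm events at the site and m is all events there. It rejects above 3.84. Each cell gives chi-square / Fisher / CMH.

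| Control rates in the two cities | Type I error, % | Power at +20 points, % | Power at +30 points, % |
|---|---|---|---|
| 40 and 40 | 5.2 / 3.4 / 5.1 | 32.5 / 23.4 / 32.5 | 62.1 / 55.2 / 62.2 |
| 35 and 45 | 5.1 / 3.3 / 5.1 | 32.4 / 23.2 / 32.5 | 62.1 / 55.3 / 62.4 |
| 30 and 50 | 4.7 / 3.1 / 5.0 | 32.1 / 22.8 / 32.8 | 62.3 / 55.3 / 63.5 |
| 25 and 55 | 4.1 / 2.6 / 5.0 | 31.6 / 22.0 / 33.8 | 62.5 / 55.4 / 66.1 |
| 20 and 60 | 3.3 / 2.1 / 5.1 | 30.7 / 20.8 / 36.3 | 62.9 / 55.5 / 70.5 |

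At a +30-point effect, chi-square power hardly moves as the gap widens. The loss there is power that the stratified test would have gained.

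**Step 3: low rates, as for PrEP.** The article's only anchor is 6% ever-use at ages 18-24. Each cell gives chi-square / CMH power.

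| Control rates in the two cities | +20 points, % | +30 points, % |
|---|---|---|
| 3 and 9 | 47.6 / 46.5 | 79.4 / 78.8 |
| 5 and 15 | 41.1 / 40.7 | 73.6 / 72.5 |

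Here the unstratified test is level or slightly ahead although the cities differ. These rows use all 60 participants; the PrEP uptake outcome is restricted to those with a behavioral indication, so its numbers would be no larger.

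**The case against.** **The test sentence may be shorthand.** It promises appropriate tests after distributions are inspected, and it also covers self-efficacy scores, for which chi-square or Fisher's test is not natural. Table 1 already lists site as a covariate, and a SAP that is not shown may specify how site enters. This stands in part: the article does not exclude a stratified analysis. But the tests it does name take no account of site, the design fixes site as a stratum, and the one adjustment rule given would pass site over. That is a mismatch in what is written, not merely an omitted detail.

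**A reader might infer that power is lost whenever the cities differ.** The documents do not support this. They give no rates by city, the loss is negligible up to about a 20-point gap, and at low event rates the sign can reverse.

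**A reader might infer that the planned standard errors and confidence intervals are too wide.** The article gives 95% CIs only for the single-arm acceptability and feasibility estimates. Fisher's test uses no standard error, and its shortfall with identical cities (55.2% against 62.2%) comes from discreteness, not from ignoring site.

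**A reader might fear false positives or a wrong decision to proceed.** The error is conservative. Study Design does name preliminary efficacy among the information that will guide the next step. The numerical minimum criteria, however, are single-arm, and the Discussion ties progression to acceptability and feasibility.

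**Conclusion.** The point holds in limited form and is minor. The named between-arm tests ignore the stratification factor, and nothing in the article brings it back. Should Boston and the Bronx differ by 30 points or more in HIV testing, chi-square gives up about 4 power points (30-point gap) to 8 points (40-point gap) against CMH at a +30-point effect, and 2 to 6 points at +20. Its type I error drops to 4.1% and 3.3%. Below about 20 points the loss is roughly 1 point or less. For PrEP-like rates no gain should be expected.

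These sizes rest on the assumed 40% mean control rate, a constant additive effect, 20:10 per site and full follow-up. Whether city gaps of 30 to 40 points are realistic cannot be judged from the article.

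**What to change.** In Statistical Analyses, state that binary outcomes are compared between arms with a Cochran-Mantel-Haenszel test stratified by SRV, reported with a Mantel-Haenszel risk difference and its stratified 95% CI. State also that models for SCT scale scores include SRV as a term.

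The change is a sentence or two, with no new data and no change in sample size. It is not entirely free:
- **Low event rates:** CMH can cost about 1 power point against chi-square, whether or not the cities differ (the largest loss in Step 3 is 47.6 − 46.5 = 1.1 points).
- **Exact version:** if an exact stratified test is used for sparse counts, it is more conservative. At a 40% rate and a +30-point effect its power is 53.1% against 55.2% for Fisher's test when the cities are alike, and 54.4% against 55.3% at a 10-point gap.

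Naming the test in advance, rather than choosing it after seeing the distributions, would settle the matter.

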### Aims and Objectives

The aim of this paper is to describe the protocol for the refinement of an HIV prevention mobile app, beta testing it, and conducting a pilot randomized controlled trial (RCT) to examine the acceptability and feasibility of the MyChoices app for YMSM. We hypothesize that participants who are randomized to use the MyChoices app will report that the app is highly acceptable and will use the main functions of the app over the follow-up period. We also hypothesize that while not powered to detect significant differences, MyChoices users will report taking more HIV tests and increasing PrEP uptake compared with YMSM receiving the control condition.

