**Secondary outcomes**			
	HIV testing		Proportion testing at least once during study
	PrEP^a^ uptake		Proportion of those with a behavioral indication for PrEP who are prescribed and utilize PrEP

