##### Secondary Outcome Measures

While this pilot study is not powered to examine the efficacy of behavioral outcomes, at each major assessment, participants will be asked to self-report on HIV testing in the previous 3-month interval. We will also assess self-report accuracy by obtaining medical release for HIV test results. Additionally, at each assessment, participants will self-report whether, in the past 3 months, they made and attended a clinic appointment for PrEP initiation, whether they were prescribed PrEP, and whether they utilized PrEP.

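### HIV testing, a secondary outcome in a pilot declared unpowered for it, is made the main efficacy test at alpha=.05 at two time points, and its 3-month recall fits the cumulative outcome poorly when the month-3 survey is missed

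*Protocol article*

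**What the plan says.** All references are to the protocol article.

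- **Status of the outcome.** Table 1 (Data Collection) places HIV testing under secondary outcomes: "Proportion testing at least once during study". The primary outcomes are app acceptability and app feasibility.
- **Power.** Aims and Objectives introduces the HIV testing and PrEP hypothesis with the words "while not powered to detect significant differences". Secondary Outcome Measures repeats the point: "While this pilot study is not powered to examine the efficacy of behavioral outcomes".
- **Analysis.** Statistical Analyses gives HIV testing the role of the primary comparison for efficacy, "defined by the proportion that self-reports at least 1 HIV test result during follow-up", made "between the study arms at 3- and 6-month follow-ups". The rule for judging it is general: "All analyses will use two-tailed tests of significance, with significance at alpha=.05". The same section states 95% confidence intervals for the mean usability score and the proportion using the app, both in the intervention arm only.
- **Measurement.** Under Secondary Outcome Measures, at each major assessment "participants will be asked to self-report on HIV testing in the previous 3-month interval". A second source is planned: "We will also assess self-report accuracy by obtaining medical release for HIV test results". Statistical Analyses compares documented test results between arms as a separate item.
- **Design.** Study Design and Randomization give 60 participants, allocated 2:1 (40 app, 20 control), followed for 6 months with a survey every 3 months.

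**The concern.** Two things fit badly together.

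The first is the way the result will be judged. The protocol says that it cannot expect to detect differences in behavior, then fixes statistical significance as the rule for every between-arm comparison. It raises one secondary outcome to a leading efficacy role and does not say whether month 3 or month 6 carries the reading. A non-significant result may be taken as no signal, and a significant one at either time point as efficacy. Neither helps to plan the larger trial, which needs an estimated difference and its uncertainty.

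The second is the data. The outcome accumulates over follow-up, but each survey looks back only 3 months. A participant who skips month 3 and completes month 6 is not asked about months 0 to 3 by the item as described. An analysis plan can choose how to handle such a gap, but it cannot supply an answer that was never requested.

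**Working it through.** **Inputs.** From the protocol: 40 and 20 participants; two-sided alpha .05; comparisons at months 3 and 6; 3-month recall. The protocol states no power or effect size, so there is no figure to reproduce; the allocation is consistent (60 × 2/3 = 40, 60 × 1/3 = 20). It also gives no expected testing rate under study conditions and no survey non-response. The values used for these below are assumptions, shown as ranges.

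**1. Precision.** With a common proportion *p*, the 95% half-width for the difference is 1.96 × √[p(1−p)(1/40 + 1/20)].

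| p | Half-width |
|---|---|
| 0.225 | 0.224 |
| 0.30 | 0.246 |
| 0.40 | 0.263 |
| 0.50 | 0.268 |

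The interval is therefore about ±22 to ±27 percentage points. The value 0.225 converts the roughly 40% annual testing implied in the Background to 6 months at a constant rate: 1 − √0.6 = 0.225.

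**2. What a p-value can show.** Exact power is the sum, over all 2×2 tables with p ≤ .05, of the product of the two binomial probabilities. For a 20-point difference with control rates of 20% to 60%, it is 23% to 32% with Fisher's test and 32.5% to 38.4% with the uncorrected chi-square test. For a doubling from 22.5% to 45%, it is 34% and 41%. Non-significance is the more likely result even then.

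**3. Two looks at one outcome.** If the two tests were independent, the chance of at least one false positive would be 1 − 0.95² = 0.0975. They are not independent, because the month-3 outcome is contained in the month-6 outcome. Simulation (200,000 runs, 20% to 40% testing per interval) gives 0.083 to 0.092 with chi-square and 0.057 to 0.062 with Fisher. The inflation is modest.

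**4. Recall window against the cumulative outcome.**

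| Surveys completed | Months asked about | Any test by month 6 |
|---|---|---|
| Both | 0–6 | Known |
| Month 6 only | 3–6 | Known if yes, open if no |
| Month 3 only | 0–3 | Known if yes, open if no |
| Neither | None | Open |

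Only the second row comes from the recall window; the third and fourth involve a missed month-6 survey, which is ordinary attrition. Let *m* be the non-response per survey and *q* the probability of testing in a 3-month interval, all independent. The undetermined share in the second row is m(1−m)(1−q):

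| | q = 0.20 | q = 0.30 | q = 0.40 |
|---|---|---|---|
| m = 0.10 | 0.072 | 0.063 | 0.054 |
| m = 0.20 | 0.128 | 0.112 | 0.096 |

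This is about 5% to 13% of participants, or roughly 3 to 8 of 60 (60 × 0.054 = 3.2; 60 × 0.128 = 7.7).

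**5. Effect on the estimate.** If these participants were counted as untested, the proportion in an arm would fall by m(1−m)(1−q)q. At the extremes this is 0.072 × 0.20 = 0.014 and 0.096 × 0.40 = 0.038, so 1.4 to 3.8 points. At q = 0.30, non-response of 10% in one arm and 20% in the other would shift the difference by 0.112 × 0.30 − 0.063 × 0.30 = 0.034 − 0.019 = 0.015, or 1.5 points.

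**The case against.** The strongest reply is that this is a pilot which openly discloses its lack of power, so low power is not an error. The primary analyses use point-estimate criteria with confidence intervals, and the abstract and Discussion condition the next trial on acceptability and feasibility. No passage makes an HIV-testing p-value a go/no-go rule, and nothing says that between-arm intervals will be withheld. Adjustment for multiple tests and rules for missed surveys commonly sit in a statistical analysis plan, which is not shown. All of that stands, and it limits the point to secondary outcomes. It does not remove the wording fixed here: the efficacy label, the two time points and the significance rule. Study Design also counts preliminary efficacy among the information that will determine whether the app goes forward.

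On recall, other sources may help: medical-release results, testing history (listed in Table 1), and photographs of results, which the Discussion says will be explored. The article assigns none of them to filling gaps. Medical release is described as a check on accuracy, and documented results are a separate comparison.

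Three stronger readings are tempting and are not supported:

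- A reader might infer that any missed survey destroys the cumulative outcome. It does not: a yes on the completed survey settles it.
- A reader might infer a large risk of false positives from testing everything at .05. For the two looks that the protocol names on this outcome, the risk is at most 9.75%. A figure for all between-arm tests would need a count that the document does not give.
- A reader might infer that Table 1 and Statistical Analyses define different outcomes. They define the same one, evaluated at two times.

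**Conclusion.** The point holds in limited form. An outcome listed as secondary, in a pilot declared unpowered for it, is given the leading efficacy role, is compared at two time points without one being named as decisive, and is judged at alpha=.05, while intervals are stated only for single-arm outcomes. With 40 and 20 participants, the informative result is a difference with an interval of about ±22 to ±27 points.

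The recall mismatch leaves the cumulative outcome undetermined for about 5% to 13% of participants, namely those who miss month 3 and answer no at month 6. This rests on assumed non-response of 10% to 20% per survey, assumed testing of 20% to 40% per interval, and independence between them. The resulting bias is small beside the sampling error, but the gap is avoidable.

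The primary outcomes and the stated condition for the next trial are untouched. The change is worth making because this comparison is the main between-arm evidence on efficacy that the pilot will produce.

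**What to change.** 1. Label the HIV testing comparison secondary or exploratory throughout.
2. Name any HIV test from baseline to month 6 as the single outcome, and show month 3 descriptively.
3. Report between-arm differences with 95% confidence intervals (Newcombe or Miettinen–Nurminen for proportions), and limit the significance rule so that these comparisons are not judged by p<.05.
4. Word the follow-up item to ask about HIV tests since the last completed survey. This closes the gap for participants who miss only month 3.

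The cost is one changed survey stem and some analysis wording. The downsides are recall of up to 6 months for those who missed month 3, and giving up significance claims on behavioral outcomes. For surveys already completed, the stem change comes too late, but items 1 to 3 still apply.
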